**a) Developing Implementation Model 0 (M0):**

The initial implementation model (M0) will be developed as a foundational framework for integrating MSUD services within NCD care. This model will include workflows, protocols, and resource allocation strategies tailored to each level of healthcare delivery, from sub-centers to tertiary hospitals. The model will draw upon existing national guidelines, such as the ICMR workflows and the mhGAP Intervention Guide by the WHO [25], as well as the insights from the formative research regarding local facilitators and barriers. Specific components will include:

◦**Screening and Assessment:** Standardized tools based on WHO’s mhGAP and ICD-11 for screening and diagnosing MSUDs among patients with NCDs [22–25].◦**Care Pathways:** Well-defined referral pathways and protocols to ensure timely diagnosis, treatment, and follow-up, considering the specific roles of ASHAs, Community Health Officers (CHOs), and Medical Officers (MOs) at different healthcare levels [24].◦**Patient Education:** Materials and engagement strategies will be developed to encourage patient participation in MSUD care.◦**Digital Platform Integration**: A digital application for tracking patients, managing referrals, and monitoring treatment adherence, which will also provide real-time data for evaluation.

**b) Mixed Methods Evaluation Using CFIR and IRLM:**

The implementation model (M0) will be evaluated using a combination of qualitative and quantitative methods, guided by the Consolidated Framework for Implementation Research (CFIR) [32] (Table 2) and the Implementation Research Logic Model (IRLM) (Table 3) [33]. These frameworks will help identify the constructs that contribute to or hinder the integration of MSUD services within NCD care across different settings. The IRLM will support mapping the inputs, activities, outputs, and outcomes, while the CFIR constructs will guide data collection on implementation processes and context.

**Table 3 pone.0332359.t003:** Pre-facility, facility, and post-facility components of the logic model and specific aspects of the logic model for the implementation framework.

	Pre-Facility	Facility		Post-facility	
Objectives	Identifying study sites Addressing stigma Human resources	Integrate screening, diagnosis, treatment, and linkage within the health system, monitoring of treatment adherence		Sustainability of screening and treatment for mental health conditions Integrated care being scaled up at the state level	
Activities	Stakeholder’s meetings Community engagement Capacity building workshops	Stakeholder’s meetings Involve policymakers Community engagement Capacity building of relevant HCWs, workshops Creating an online platform for seamless data collection and integration		Identify barriers of sustainability and scaling up Collaboration with policymakers and other stakeholders Budgetary allocation	
Personnel involved	Policymakers, health department, community leaders, HCW	ASHA workers, ANM, CHO, MO Private doctors		Policymakers Health department officials	
Outcomes	Increased public awareness and reduced stigma Availability of trained human resources	At least 70% screening for target mental health conditions among people seeking care for NCD At least 70% of those screened positive, get appropriate treatment and linkage to care. Screening and treatment are acceptable, feasible, adoptable, and affordable		Adoption and scaling up of the integrated care at the state level	
**Specific aspects of the logic model for the implementation framework**					
**Target population**	**Underlying assumptions**	**Resources and challenges**	**Activities (input)**	**Output**	**Outcomes**
Persons with NCD seeking treatment at the health facilities Beneficiaries Persons with NCD and comorbid target mental illness and tobacco and alcohol misuse	Theoretical assumption of how the program will work? It is possible to train the existing HCWs and integrate screening, treatment, and linkage to higher services	ANMs, CHO, PHC MOs, GPs (private hospitals)	Training and capacity building for existing HCW cadre to deliver the intervention package Establishing a monitoring system Training of a cadre in the existing healthcare system in monitoring Periodic quantitative and qualitative monitoring Advocacy Additional funds and resource allocation	Number of persons with NCD screened, identified with target mental health conditions, treated, and successfully linked at various health care levels	• % screened • % identified with mental health conditions • %treated as per the guideline • % successfully linked with higher services • % retained in the treatment • Generating a cascade of care with a target at least 70% at each level • Acceptability, feasibility, Adoption, fidelity, implementation cost of the program

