### Aims & objectives

The aims of the study are to develop, assess the feasibility, implement a service delivery model to achieve high coverage (≥70%) of screening, management, and linkage to care of common mental disorders (CMDs) and substance use disorders (SUDs) among individuals seeking care for non-communicable diseases (NCDs) at public health facilities and to evaluate the cost associated with the implementation of the proposed service delivery model.

The primary objective is to develop and implement a service delivery model that would result in high coverage (at least 70%) of screening, management, and linkage to care of common MSUDs among persons seeking care for NCDs at public health facilities. The secondary objectives are to (a) assess the feasibility of adoption of the implementation model by the health care system and (b) evaluate the costs of the mental health service strengthening intervention package from the health system as well as the patient’s perspective.

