In **Phase III**, the final model shall be implemented across the district at each of the sites. The primary evaluation outcome is facility-level coverage of the mental health screening and management strategy. We require an estimate of coverage of 70% with an absolute precision of ±10% and 95% confidence. Using the single-proportion formula n = Z^2^ p (1 − p)/ d^2^, with Z = 1.96, p = 0.70, and d = 0.10, gives n = 80.7, rounded up to 81 health facilities per district. The implementation cascade was designed such that screening, referral, and management rates of ≈90% at each step yield an overall coverage of 0.9 × 0.9 × 0.9 = 0.729 (≈72.9%), which is slightly conservative with respect to the 70% target. Because the primary unit of analysis is the facility, this sample-size calculation does not require an intra-cluster correlation correction; however, if analyses are to be performed at the individual level or if clustering is a concern, the sample will be inflated by an appropriate design effect (DEFF = 1+ (m − 1) ρ), and allowance will be made for anticipated non-response. A sensitivity analysis using DEFF values between 1.2 and 1.5 and a 10% non-response adjustment is presented in Supporting Information S1 Table. (S1 Table – Sensitivity Table using Appropriate Design Effect)

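### The 70% coverage target behind the primary objective means end-to-end coverage in the sample-size section but 70% per step in Table 3, and nothing reconciles the two

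*Protocol article*

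**What the plan says.** Four parts of the protocol article bear on what the 70% measures.

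- **Aims & objectives.** The model is to achieve "high coverage (at least 70%) of screening, management, and linkage to care of common MSUDs among persons seeking care for NCDs". This can mean 70% on each component or 70% on all of them jointly.
- **Sample size (Phase III).** "We require an estimate of coverage of 70% with an absolute precision of ±10% and 95% confidence", which "gives n = 80.7, rounded up to 81 health facilities per district". The section then describes a cascade of screening, referral and management at about 90% each, multiplies the three to 72.9% overall, and calls the result one "which is slightly conservative with respect to the 70% target". The quantity compared with 70% is the product.
- **Table 3 (logic model).** The facility outcomes are at least 70% screened among people seeking NCD care, and then "At least 70% of those screened positive, get appropriate treatment and linkage to care". The second part of the table adds "Generating a cascade of care with a target at least 70% at each level". The quantity compared with 70% is each step on its own denominator.
- **Study outcomes, Primary outcomes.** Three proportions are listed: screened among NCD care seekers, linked among screen-positives, and starting treatment among those linked. No end-to-end proportion appears.

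The Discussion and Conclusion repeat the 70% figure without saying which meaning applies.

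**The concern.** The study is single-arm with no control group, so its main conclusion rests on where observed coverage lies relative to 70%. If the figure can be read as a product or as a per-step value, the same data can be reported as reaching the target or as falling well short of it, and the choice can be made after the data are seen.

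The meaning also matters earlier. The Phase 2 section continues model iterations until a model shows high coverage, among other properties, and the objective equates high coverage with at least 70%. The ambiguity therefore affects when optimisation stops as well as how Phase III is summarised.

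**Working it through.** **Inputs.** Sample size section: Z = 1.96, p = 0.70, d = 0.10, and three steps at about 0.90. Table 3: 0.70 at each step, shown as two stages in the facility outcomes. Primary outcomes: three steps with conditional denominators.

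**1. The plan's own figures.**
- n = Z²p(1 − p)/d² = 1.96² × 0.70 × 0.30 / 0.10² = 80.67, rounded up to 81. Over seven districts, 81 × 7 = 567. Both reproduce.
- 0.9 × 0.9 × 0.9 = 0.729. This reproduces.

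**2. What the per-step target implies end-to-end, using the same multiplication.**
- Three steps at the target: 0.7³ = 0.343, which is 70 − 34.3 = 35.7 points below 70%.
- Table 3's two stages at the target: 0.7² = 0.49, which is 21 points below 70%.

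**3. What the end-to-end target implies per step.**
- Three equal steps: 0.7^(1/3) = 0.888.
- Two equal steps: 0.7^(1/2) = 0.837.
- Check: 0.88³ = 0.681, so 88% at all three steps still falls short of 70% end-to-end.

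**4. How the two targets relate.** No factor exceeds 1, so a product of at least 0.70 forces every step to at least 0.70. The end-to-end target therefore implies the per-step target, but not the reverse.

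| Steps | Per-step 70% | End-to-end 70% |
|---|---|---|
| 90/90/90 | met | met (72.9%) |
| 88/88/88 | met | missed (68.1%) |
| 70/70/70 | met | missed (34.3%) |

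With three steps, whenever each lies between 70% and just under 88.8%, the per-step target is met and the end-to-end target is missed, whether or not the steps are equal.

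**5. Effect on the sample size.** If end-to-end coverage were 34.3%, ±10 points would need 1.96² × 0.343 × 0.657 / 0.01 = 86.6, that is 87 facilities, and 81 would give ±10.3 points. At 49%, 81 would give ±10.9 points. The planned precision barely depends on which meaning is chosen.

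**Assumption in steps 2 to 4.** The screening rate uses all NCD care seekers; the later rates use screen-positives or those linked. The product is end-to-end coverage of affected patients only if being screened is unrelated to having a disorder and the screen detects the cases. The Sample size section multiplies in the same way.

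**The case against.** The best defence is that the outcome list largely settles the matter. The three primary outcomes are step proportions, they agree with Table 3, and the odd one out is a single planning sentence in the Sample size section. All three proportions will be reported, so any reader can multiply them and nothing is hidden. This has weight: it shows that results would not be concealed. It does not settle which quantity the 70% objective refers to, and the sentence in question is the one that links the design to that target.

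It can also be said that each level in Table 3 might mean each tier of facility, since the neighbouring output cell speaks of health care levels. Even so, the facility outcomes in the same table still set 70% for screening and 70% among screen-positives separately.

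Some stronger readings are tempting but not supported.
- A reader might infer that the two meanings exclude each other. They are nested, and the planned 90/90/90 cascade satisfies both.
- A reader might infer a pass/fail rule. The protocol speaks of a target and sizes the study for precision. Probabilities of passing in a district, or a required lower confidence limit, would test criteria that the plan does not state.
- A reader might infer that the percentage identified with a mental health condition must also reach 70%, against the 9.3–23% comorbid depression cited in the Introduction. That item is a separate bullet with no denominator, and the cited range covers depression only, whereas the study also covers anxiety, alcohol and tobacco.
- A reader might set the 2.9-point excess of 72.9% over 70% against the ±10-point precision. The first compares a planned rate with a target and the second is sampling error, so this does not show the sentence to be wrong.

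**Conclusion.** The point holds as an inconsistency in the current text. The 70% target is end-to-end in the Sample size section and per step in Table 3, the primary outcomes contain only step proportions, and the objective fits either reading. The per-step meaning is much the weaker: at its limit it corresponds to about 34% end-to-end over three steps, or 49% over Table 3's two stages, while 70% end-to-end needs about 89% at each of three steps. These sizes rest on the step rates multiplying across different denominators.

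The 81-facility arithmetic is correct and is not in question. What needs settling is the quantity that the 70% describes, because the conclusion on the primary objective depends on it.

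**What to change.** Before Phase III results are seen, state one meaning of the 70% target, either end-to-end or per step, and give the denominator of each proportion. Use that meaning consistently in Aims & objectives, Sample size, both parts of Table 3 and Primary outcomes. Whichever is chosen, report both the step proportions and the end-to-end coverage.

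- If end-to-end is chosen, define that proportion among the outcomes and say that it calls for about 89% at each of three equal steps.
- If per step is chosen, remove the comparison of 72.9% with the 70% target from the Sample size section and state the end-to-end coverage implied by 70% at each step.

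The change is one of wording. The number of facilities need not change on this account. The downside is that the headline coverage claim may become harder to make.

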**c) Logic Model Development for Process Monitoring:**

A logic model will be developed to monitor the implementation processes and outcomes. This model will include:

Inputs (resources, staff, infrastructure)Activities (training, patient screening, referral)Outputs (number of patients screened, treated, and followed up)Outcomes (improvements in mental health service coverage and patient health metrics). Regular meetings with site investigators and key stakeholders will help refine the logic model based on observed challenges and successes.

**d) Model Optimization through Iterative Pilot Testing:**

The initial model (M0) will be piloted in a sample of healthcare facilities, including selected AAMs, PHCs, CHCs, and Taluk Hospitals (or District Hospitals if available) within the designated districts. This pilot study will allow the research team to test the feasibility and effectiveness of the intervention package under real-world conditions. (Tables 4 and 5) Key activities during pilot testing will include:

**Table 4 pone.0332359.t004:** Human resources, service delivery, and infrastructure focus during the pre-integration, integration, and post-intervention.

	Pre-integration of NCD and mental health care	Integrated NCD and mental healthcare	Post-intervention (sustenance)
**Human resources**	• Training and capacity building of the target human resource • Developing cadres of trainers • Developing a cadre of monitoring masters	• Ongoing training, capacity building, and feedback of newly recruited human resources • Experiential ongoing training by the field research staff	• The master trainer cadre continues the training and capacity-building work.
**Service delivery**		• Screening, treatment, and linkage (STL) to care/adhering to the care cascade for the target mental health conditions in persons with NCD • Integrated and seamless record collection and periodic monitoring (and feedback)	• STL continues • Periodic monitoring continues by the district health department (by the monitoring masters).
**Infrastructure/logistics/supplies**	• Designing the digital platform/app for seamless and integrated implementation and data collection and monitoring • Developing training modules for master trainers and HCWs	• Human resources (field coordinator for supervision, monitoring, and quality assurance, and for data analysts) • Support to continue to provide incentives to the HCWs • Ongoing technical support for app development, piloting, and maintenance	• Additional budget allocation for sustenance of the service

**Table 5 pone.0332359.t005:** Nine aspects of concept mapping as suggested in the Expert Recommendations for Implementing Change (ERIC) that shall be utilized during Phase 2.

Using evaluative and iterative strategies	We will be developing a formal implementation blueprint, and it will be re-examined based on the feedback and suggestions given by the stakeholders. We will also be conducting regular audits and adapting the feedback to improve the implementation. We will be developing and organizing quality monitoring systems and implementing tools for the same.
**Providing interactive assistance**	We will be providing centralized assistance to all the centers for any technical and implementation aspects. Also, the clinicians will be supported through a collaborative care model.
**Adaption and tailoring to context**	We will promote adaptability and tailor implementation strategies based on the expert inputs.
**Developing stakeholder interrelationships**	We will be networking with the local panchayat or government leaders and informing the local opinion leaders. We will conduct regular meetings with them and update them about the developments in the implementation.
**Training and educating stakeholders**	Workshops/meetings will be conducted involving state government officials and experts from study sites, including regional and district health offices, health facilities, and implementing partners. The workshop will orient stakeholders and strengthen local partnerships for successful implementation of project activities.
**Supporting HCWs**	The HCWs will be provided training on the service delivery model, which will include educational materials, treatment guidelines, protocols, communications, digital app and tools for successful implementation.
**Engaging patients and caregivers**	Patients and caregivers will be engaged from the formative research till the end of the study to get opinions on the implementation of the service delivery model. Given educational materials and awareness, mental health will be provided.
**Utilizing financial strategies**	A review of financial strategies to innovate on financial schemes or incentives to be evaluated in each site shall be considered.
**Changing infrastructure**	Necessary changes to the infrastructure in terms of changing physical structure and equipment and recording systems will be requested.

◦Training and Capacity Building: Health workers (ASHAs, CHOs, and MOs) will receive targeted training on MSUD screening, assessment, and treatment protocols, as well as on the use of digital tools for patient tracking.◦Workflow Refinement: Feedback from healthcare providers will be gathered to refine workflows, screening protocols, and referral pathways, ensuring the model is efficient and adaptable across various settings.◦Stakeholder Engagement: Regular feedback loops with healthcare providers, administrators, and community representatives will help address practical barriers and enhance local buy-in.

#### Phase-2 – model optimization.

In Phase-2, based on the insights gained from pilot testing, subsequent iterations of the model (e.g., M1, M2…Mx) will be developed to improve coverage and quality of MSUD services. Each iteration will incorporate lessons learned from previous cycles, such as adjustments to training content, improvements to digital tracking tools, and enhanced patient engagement strategies. These iterative cycles will continue until a model is identified that demonstrates high coverage, feasibility, and effectiveness across all levels of the healthcare system.

#### Continuous stakeholder feedback and model adaptation.

Throughout the optimization process, feedback from all stakeholders, including healthcare providers, patients, and local health officials, will be actively solicited. This feedback will guide adjustments to the model, ensuring it remains responsive to the needs of the healthcare workers and patients. Workshops and collaborative sessions will allow stakeholders to reflect on the model’s performance, share experiences, and contribute to its ongoing refinement.

#### Integration of CFIR constructs for process evaluation.

During each cycle of model development and optimization, CFIR constructs will guide the process evaluation, ensuring comprehensive assessment of implementation processes. Constructs such as intervention characteristics (e.g., complexity, adaptability), outer setting (e.g., external policies, patient needs), inner setting (e.g., culture, implementation climate), and individual characteristics (e.g., knowledge, beliefs) will help identify factors impacting the effectiveness and sustainability of the model. These evaluations will ensure that any final model is evidence-based, contextually relevant, and scalable across other regions.

#### Phase-3-full implementation and evaluation.

The optimized implementation model finalized in Phase II shall be implemented across all the healthcare facilities across all the selected districts. We will continue to use the nine aspects of concept mapping as suggested in the Expert Recommendations for Implementing Change (ERIC) [34] while implementing the optimized model across the selected Taluks or the whole district.

The implementation support team (the research team) will continue to be active in the capacity of facilitator and advisor to the implementation teams (HCWs engaged in care delivery). There will be ongoing mentorship and quality improvement feedback cycles within each facility. Implementation activities will include ensuring access to and use of the intervention package, the digital platform, and the application; HCW training; community awareness and demand generation; establishment of referral and supervision systems; monitoring; and continuous feedback loops.

#### Process monitoring.

The program learning team will slowly transition to documenting implementation processes by measuring the process indicators. The Process indicators for service delivery implementation are described in Table 6.

**Table 6 pone.0332359.t006:** Key process indicators for service delivery implementation.

Component	Purpose	Formative Uses	Summative Uses	Assessment tools
Fidelity (quality)	Extent to which intervention was implemented as planned.	To assess the Monitor and adjust program implementation as needed to ensure theoretical integrity and program quality	• Proportion of health facilities integrated with mental health with NCDs	• Quality check using the CHO/MO in each of facility once a month
Dose delivered (completeness)	Amount or number of intended units of each intervention or component delivered or provided by interventionists.	To plan number of facilities the service delivery will be implemented	• Number of trainings conducted for ANM/ ASHA on screening and referral for MSUD among patients with other NCDs • Number of trainings conducted for CHO on screening, management and referral for MSUD among patients with other NCDs • Number of trainings conducted for MOs on assessment, management of MSUD among patients with other NCDs • Number of training sessions conducted for ANM/ASHA/ CHO/ community leaders on patient education and engagement to raise awareness and promote shared decision-making	• Numerators and denominators
Dose received (exposure)	Extents to which participants actively engage with, interact with, are receptive to, and/or use materials or recommended resources;	To monitor and take corrective action to ensure participants are receiving and/or using materials/resources.	• Number of training sessions attended by ANM/ ASHA to do screening and referral for MSUD among patients with other NCDs • Number of training sessions attended by CHO to do screening management and referral for MSUD among patients with other NCDs • Number of training sessions attended by MO to do assessment, management of MSUD among patients with other NCDs • Number of training sessions attended by ANM/ASHA/ CHO/ MO on Digital App • Number of training sessions attended by ANM/ASHA/ CHO/ community leaders on patient education and engagement to raise awareness and promote shared decision-making	
Dose received (satisfaction)	Participant (primary and secondary audiences) satisfaction with program, interactions with staff and/or investigators	To obtain regular feedback from health care workers and use feedback as needed for corrective action.	• Pre and post-tests will be conducted using a questionnaire to understand the satisfaction of the Health care workers following the training programme. • Based on the scores obtained by them personalized feedback will be given and booster sessions will be given to those low scores.	• Pre and posttest for ANM/ ASHA training • Pre and posttest for CHO training • Pre and posttest for MO • Pre and posttest for Digital App training for ANM/ ASHA • Pre and posttest for Digital App training for CHO • Pre and posttest for Digital App training for MO
Reach (participation rate)	Proportion of the intended priority audience that participates in the intervention; often measured by attendance; includes documentation of barriers to participation.	Monitor numbers and characteristics of participants; ensure sufficient numbers of target population are being reached.	• Proportion of health facilities from where the HCWs were trained on screening, management and referral for MSUD among patients with other NCDs • Proportion of health facilities from where the HCWs were trained on Digital App • Proportion of ANM/ ASHA trained in screening and referral for MSUD among patients with other NCDs • Proportion of CHO trained in screening, management and referral for MSUD among patients with other NCDs • Proportion of MO trained in assessment, management of MSUD among patients with other NCDs • Proportion of ASHA/ ANM trained on Digital/App • Proportion of CHO trained on Digital App • Proportion of MO trained on Digital App • Proportion of ANM/ ASHA/ CHO community leaders, trained on Patient education and engagement to raise awareness and promote shared decision-making	• Attendance Sheets for all training programs • Reasons documented for why participants did not attend the training
Recruitment	Procedures used to approach and attract participants at individual or organizational levels; includes maintenance of participant involvement in intervention and measurement components of study.	Monitor and document recruitment procedures to ensure protocol is followed; adjust as needed to ensure reach.	• Recruitment of the Health care workers for the training will be based on the list provided by the District Health Officer. • Persons aged 18 years and above, being screened for NCDs or diagnosed with NCD	• Number of requests placed with district administration for training of ANM/ ASHA/ CHO/ MO • Proportion of ANM/ ASHA invited to participate in the training sessions • Proportion of CHO invited to participate in the training sessions • Proportion of MO invited to participate in the training sessions • Proportion of ANM/ ASHA contacted telephonically/ personally to ensure participation in the training programs • Proportion of CHO contacted telephonically/ personally to ensure participation in the training programs Proportion of MO contacted telephonically/ personally to ensure participation in the training programs
Context	Aspects of the environment that may influence intervention implementation or study outcomes; includes contamination or the extent to which the control group was exposed to the program.	To monitor aspects of the physical, social, and political environment and how they impact implementation and needed corrective action.	• The environmental aspects which can affect the service delivery implementation or outcomes will be ascertained during the formative research and then the solutions would be obtained during the model optimizations and then the intervention will be delivered • Also to prevent contamination, each phase of the study would be done in only one or two blocks/wards	• Number of additional trainings on MSUD carried out in the district besides the training as part of the Project ICMR • Organization that conducted the training • Details of the content, duration, venue (online/ offline), trainers for the training (psychiatrist/ psychologist/ others) disorders covered, type of interventions converted (screening, assessment, management, referral, etc.) for training • Number of the HCWs (ANM, ASHA, CHO, MO) from the block included in the phase II who attended the training

We shall also collect the data with the aim to evaluate the implementation of the optimized model based on the outcome measures. Our evaluation shall be based on the RE-AIM framework (Evaluation) and Implementation Research Logic Model (Evaluation) [33].

